**University of Auckland**

**[name] PhD**

**Department of Biochemistry**

**University of Otago**

The genome-wide association studies (GWAS) of serum urate and fractional excretion of uric acid (FEUA) have consistently reported a strong association with common variants of *SLC2A9* and *ABCG2* [4-8]. The Genetics of Gout in Aotearoa study has strongly implicated the *SLC2A9* gene in development of gout in Māori and Pacific people (odds ratios  $\geq 5.0$ ) [9]. Variation in the *rs11942223* *SLC2A9* single nucleotide polymorphisms (SNP) was most strongly associated with gout in Māori, Pacific and Caucasian case-control cohorts in this study. Between 31.7%-47.2% of control participants possessed at least one protective alleles (i.e. 1/2 and 2/2 genotypes)

*ABCG2* encodes the cellular efflux pump breast cancer resistance protein (BCRP). An *ABCG2* variant (*rs2231142*, *Q141K*) is strongly associated with gout and hyperuricaemia, and is thought to regulate serum urate concentrations through extra-renal (gut) underexcretion [10]. In addition, *ABCG2* variants play a role in treatment responses to allopurinol (a purine xanthine oxidase inhibitor), and BCRP can transport allopurinol [11].

Our recent studies of acute fructose loading have shown that *SLC2A9* and *ABCG2* variants influence changes in serum urate, serum glucose changes and fractional excretion of uric acid (FEUA) in response to a fructose load [12, 13]. It is unknown whether these effects occur due to direct interactions with fructose, or whether these effects are non-specific responses to hyperuricaemia induced by fructose. Here, we aim to examine the role of *SLC2A9* and *ABCG2* variants on serum urate responses and renal urate handling in response to an acute inosine load.

### **PRIMARY HYPOTHESIS**

That individuals possessing at least one protective allele at *SLC2A9 rs11942223* have a lower hyperuricaemic response to an inosine challenge.

### **KEY SECONDARY HYPOTHESIS**

That individuals possessing at least one *ABCG2 141K* variant have a higher hyperuricaemic response to an inosine challenge.

## **3. STUDY SYNOPSIS**

Intervention study to examine the influence of genetic variation on inosine-induced hyperuricaemia. The primary endpoint is change in serum urate over 180 minutes after inosine ingestion. Key secondary and exploratory endpoints are change in fractional excretion of urate. The key genes of interest are *SLC2A9* (GLUT9) and *ABCG2*. However, other genes associated with purine synthesis and urate transport may also be examined in later exploratory analyses. This protocol is modified from previous our previous short term studies investigating the acute effect of skim milk and fructose on urate concentrations and renal excretion of uric acid in healthy volunteers [13, 14].

## **4. PARTICIPANT SELECTION**

### **4.1. Summary**

100 healthy participants without documented gout (50 of European Caucasian ancestry and 50 of Māori or Pacific ancestry).

#### **4.2. Recruitment**

Participants will be recruited by public advertising.

#### **4.3. Inclusion criteria**

- a. Able to provide written informed consent
- b.  $\text{eGFR} > 60 \text{ mL/min/1.73 m}^2$

#### **4.4. Exclusion criteria**

- a. History of gout
- b. History of kidney stones
- c. History of diabetes mellitus
- d. Diuretic use
- e. Urine pH  $\leq 5.0$  (risk factor for uric acid urolithiasis)

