## 11. STUDY PROTOCOL SUMMARY

| Visit No.                                           | 1      | 2     |
|-----------------------------------------------------|--------|-------|
| Visit type                                          | Screen | Study |
| Informed consent                                    | √      |       |
| Inclusion/exclusion criteria                        | √      |       |
| Laboratory tests (eGFR, urine pH testing)           | √      |       |
| Confirm fasting status                              |        | √     |
| Relevant medical history recorded                   |        | √     |
| Detailed family history recorded                    |        | √     |
| Ancestry recorded                                   |        | √     |
| Weight, height, waist circumference                 |        | √     |
| Blood pressure                                      |        | √     |
| Insert venous catheter                              |        | √     |
| Baseline blood and urine testing, including for DNA |        | √     |
| Administer inosine tablets                          |        | √     |
| Serial blood and urine testing                      |        | √     |
| Remove venous catheter                              |        | √     |
| Record adverse events                               |        | √     |

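### The eligibility list and screening steps do not address pregnancy or breastfeeding, although women may enrol and take an inosine load with no stated benefit to them (low priority, precautionary)

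*Protocol*

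**What the plan says.** Section 4.2 opens recruitment to the public: "Participants will be recruited by public advertising". Section 4.1 describes the target population as healthy people without documented gout, half of European Caucasian and half of Māori or Pacific ancestry. It sets no limit on sex or age.

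Section 4.3 has two inclusion criteria: "Able to provide written informed consent", and an eGFR above 60 mL/min/1.73 m². Section 4.4 has five exclusions: "History of gout", "History of kidney stones", "History of diabetes mellitus", use of diuretics, and a urine pH of 5.0 or below. The last is explained as a "risk factor for uric acid urolithiasis".

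The section 11 table lists eGFR and urine pH as the screening laboratory tests. Section 6.3 has participants fast overnight, take 1.5 g of inosine and stay fasted while blood is drawn up to 180 minutes. Section 7 supports the dose by pointing to other inosine trials and to the recommended daily range.

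**The concern.** The two lists in sections 4.3 and 4.4 are the whole eligibility rule. If they are applied as written, a pregnant or breastfeeding volunteer who consents, passes the eGFR and urine pH checks and has none of the listed conditions is enrolled and given the test substance.

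The study is a physiological challenge in healthy volunteers, and the protocol states no benefit to any of them. A competent adult can accept that for herself. In this group the exposure may also reach a fetus or an infant, and the protocol does not consider that. Eligibility belongs in the protocol, so the gap cannot be regarded as left to a statistical analysis plan.

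**Working it through.** No figure in the plan bears on this point, so the check is a reading of every place where pregnancy or breastfeeding could be caught.

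1. **Inclusion criteria (4.3).** Consent and eGFR. Items addressing pregnancy or breastfeeding: 0 of 2.
2. **Exclusion criteria (4.4).** Gout, kidney stones, diabetes, diuretics, urine pH. Items: 0 of 5.
3. **Screening laboratory tests (11).** eGFR and urine pH. Items: 0 of 2.
4. **Screening visit (6.2).** Consent and a check of the criteria above. It adds no criterion of its own.
5. **Baseline history (6.5a).** Past medical history, medications, allergies, alcohol, family history of gout and ancestry. Pregnancy and lactation are not named. This history is taken at Visit 2, and a volunteer who mentioned a pregnancy then would still meet no exclusion.
6. **Study-visit laboratory tests (8.1 to 8.3).** Urate, creatinine, glucose, stored samples, DNA and urine volume. No pregnancy test.

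The next question is whether such a volunteer could realistically present. Sections 4.1 to 4.4 set no sex or age limit, and recruitment is by public advertisement. Section 9.2 plans comparisons by age and sex, so both sexes are expected.

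The third question is whether the protocol's case for the dose reaches this group. Section 7 cites earlier inosine trials, the recommended daily range, and a mean urate rise of 0.18 mmol/L (SD 0.07) at a mean dose of 1.53 g in a long-term Parkinson's disease study. It says nothing about pregnancy or lactation.

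The visit also involves fasting and a blood volume of 30 + 5 × 15 = 105 ml (section 6.4).

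Finally, timing. Section 6.1 allows the visits to be on the same day or up to two weeks apart. An answer given at Visit 1 can therefore be out of date by the time of ingestion.

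**The case against.** **The volunteers are described as healthy.** Sections 4.1 and 9.1 use the word but never define it beyond the criteria. A woman with an uncomplicated pregnancy may fairly be called healthy, so the word does not close the gap.

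**The documents show no harm.** This stands. Nothing in the protocol describes a risk of inosine in pregnancy or lactation. The exposure is a single dose of a product sold by health food suppliers. Having no stated benefit is common to every volunteer here. The point therefore rests on precaution and on the silence of section 7, not on a demonstrated hazard.

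**Other safeguards exist.** Ethics approval is required before the start (section 10), and the consent material was not available to this review, so a caution there cannot be ruled out. It would still not be an eligibility criterion.

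**A stronger reading is tempting.** A reader might infer that pregnant participants would distort the results because the trial measures renal function. The documents do not support this:

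- Renal function is not an endpoint. The endpoints are change in serum urate (5.1) and change in fractional excretion of urate (5.2). Creatinine clearance enters only as the denominator of the latter, and eGFR is only an entry test.
- The documents do not say how pregnancy would affect change in fractional excretion, so calling such a participant an outlier would rest on outside knowledge.
- Section 9.2 analyses change from baseline with the baseline value as covariate, which takes up at least part of any stable difference between people.
- The documents give no sex split, no expected number of pregnant volunteers and no expected displacement in urate, so any computed bias would rest on invented inputs.

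**Conclusion.** The omission is real and can be checked in full: no criterion, screening test or named history item addresses pregnancy or breastfeeding, and the rules as written would admit such a volunteer. The conclusion assumes only that the lists in sections 4.3 and 4.4 are complete, as they appear to be, and that women can enrol, which section 9.2 implies.

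It supports a precautionary participant-safety improvement and nothing more. It does not threaten the hypotheses, the power or the validity of either endpoint. Priority is low.

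**What to change.** Add to section 4.4 an exclusion for volunteers who are currently pregnant or breastfeeding, by self-report. Ask about it at Visit 1 with the other history-based exclusions, and ask again before ingestion when the two visits fall on different days. Add a matching entry to the section 11 table.

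The cost is one screening question, sometimes asked twice, and a few volunteers lost. Dose, sampling, endpoints and analysis do not change. The limitation is that self-report would miss an unrecognised pregnancy, so the change reduces the gap without closing it.

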### **5. STUDY ENDPOINTS**

#### **5.1. Primary Endpoint**

Change from baseline in serum urate concentration over 3 hours following an inosine challenge

#### **5.2. Secondary Endpoint**

Change in fractional excretion of urate to 3 hours following an inosine challenge. (The fractional excretion of urate is the ratio between the renal clearance of urate and the renal clearance of creatinine, expressed as a percentage).

### **6. STUDY VISITS**

#### **6.1. Summary of study visits**

The protocol describes two visits. The study visit will occur within two weeks of the screening visit. The screening visit and study visit may be completed on the same day, depending on participant preference.

#### **6.2. Visit 1: Screening visit**

- a. Discuss study and obtain written informed consent
- b. Check inclusion and exclusion criteria met.

### 6.3. Visit 2: study visit summary

At the study visit, a venous catheter will be inserted for blood collection. Following an overnight fast, subjects will consume the inosine tablets (1.5g, Source Naturals Inosine) with 500ml water between 0800 and 0900. Blood will be obtained for urate, creatinine, and serum storage, prior to ingestion and then 15 minutes, 30 minutes, 60 minutes, 120 minutes, and 180 minutes after ingestion. Blood will also be obtained for DNA extraction at baseline. Urine volume will be measured and urine will be obtained at these time points (with the exception of 15 minutes post-ingestion) for testing of urate and creatinine. Participants will remain otherwise fasted for the remainder of the study visit and will be given a light meal after removal of the intravenous catheter.

### 6.4. Visit 2: study visit timeline

| Time                              | Baseline
(0800-
0900) | Product
ingestion | 15 minutes
from
ingestion | 30 minutes
from
ingestion | 60 minutes
from
ingestion | 120 minutes
from
ingestion | 180 minutes
from
ingestion |
|-----------------------------------|-----------------------------|----------------------|---------------------------------|---------------------------------|---------------------------------|----------------------------------|----------------------------------|
| Insertion of iv
cannula        | x                           |                      |                                 |                                 |                                 |                                  |                                  |
| Completed
intake of
inosine |                             | x                    |                                 |                                 |                                 |                                  |                                  |
| Blood sample                      | 30ml                        |                      | 15ml                            | 15ml                            | 15ml                            | 15ml                             | 15ml                             |
| Urine sample                      | x                           |                      |                                 | x                               | x                               | x                                | x                                |
| Water
ingestion                |                             | 500ml                |                                 | Equivalent to
urine volume   | Equivalent to
urine volume   | Equivalent to
urine volume    | Equivalent to
urine volume    |

### 6.5. Visit 2: Study visit details

- a. Baseline data obtained
  - History: past medical history, medications, allergies, alcohol history
  - Family history of gout (detailed)
  - Ancestry (self-reported, and recording of the ancestry of each grandparent)
  - Clinical examination: weight, height, waist circumference and blood pressure
- b. Confirm fasting status
- c. Venous catheter inserted
- d. Baseline blood and urine samples obtained including blood for DNA extraction
- e. Inosine tablets taken with 500ml water
- f. Blood samples obtained at 15, 30, 60, 120 and 180 minutes

- g. Urine samples obtained at 30, 60, 120 and 180 minutes
- h. Water ingestion (volume equivalent to urine volume) at 30, 60, 120 and 180 minutes
- i. Venous catheter removed
- j. Light meal given

## **7. TEST SUBSTANCE**

The test substance is inosine tablets (3x500mg tablets, Source Naturals Inosine). Each tablet supplement contains 500mg inosine, 30mg calcium, plus dibasic calcium phosphate, sorbitol, stearic acid, modified cellulose gum and magnesium stearate. This supplement is available from Health Food suppliers. The dose of 1.5g is consistent with doses used in other clinical trials of inosine [1, 2] and is within the recommended daily dose range. In a long-term study of inosine in Parkinson's disease, a mean (SD) urate increase of 0.18 (0.07) mmol/L was observed with a mean dose of 1.53g inosine [1].

## **8. LABORATORY TESTING**

### **8.1. Baseline blood sample**

- a. Urate
- b. Creatinine
- c. Glucose
- d. **Plasma stored for purine and other metabolites**
- e. DNA for testing of *SLC2A9* and *ABCG2* variants, other genes involved in purine synthesis and urate transport

### **8.2. Blood samples at all other times points**

- a. Urate
- b. Creatinine
- c. Glucose
- d. **Plasma stored for purine and other metabolites**

### **8.3. Urine samples at baseline and all other timepoints (except 15 minutes post ingestion)**

- a. Urate
- b. Creatinine
- c. Volume recorded
- d. Urine stored for purine and other metabolites

## **9. STATISTICAL CONSIDERATIONS**

### **9.1. Justification of Sample Size and Study Population**

We plan to recruit 100 healthy subjects without documented gout; 50 participants of Māori or Pacific ancestry and 50 participants of Caucasian ancestry. We have chosen to pool Māori and Pacific participants into a single group of Polynesian ancestry, as the allele frequencies for *SLC2A9* are very similar in these two groups, and our previous data also indicate similar renal responses to hyperuricaemia in Māori and Pacific participants [13]. Sample size calculations have been based on the variability of change in serum urate at each time point in our previous study of fructose induced hyperuricaemia [13] and an analysis of inosine use for Parkinson's disease [1]. We have selected the *SLC2A9* SNP *rs11942223* for the primary analysis, and assume that approximately 30% of participants will have the protective allele based on our previous work in the Genetics of Gout in Aotearoa study [9]. The variability in the change in serum urate to fructose load [13] was consistent within groups with and without protective alleles across all time points (SD 0.03 mmol/l). With 70 participants without the protective allele and 30 with the protective allele the proposed study is adequately powered (90% at the 5% significance level for a two tailed test) to detect a difference in the change in serum urate between these groups of at least 0.02mmol/l.

We wish to perform a subgroup analysis using Māori or Pacific and Caucasian case-control cohorts, and have powered the study based on the above assumptions. Here we will recruit 50 participants of each ancestry, and estimate that 14-16 participants within each ancestral group will have the protective allele. In the smallest group comparison, n=16 vs. n=34 within an ancestral subgroup, there is in excess of 90% power (at the 5% significance level for a two tailed test) to detect a difference in the change in serum urate 180 minutes after an oral inosine challenge of at least 0.03 mmol/l. Pooled factorial secondary analyses will therefore similarly be adequately powered for the same effect size.

Whilst the primary analysis will be performed on the change from baseline, no adequate estimate of the variability of this is available and so the conservative approach of modelling the difference between groups at a single time point was chosen to validate the sample size. Removing between patient variability by using the change from baseline as the dependent variable is likely to offer increased power which should more than offset the very small number of samples which may not be adequately genotyped. Sample size calculations were performed using PASS 2002 (Hintze, J (2006) Kaysville, Utah).

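### The 90% power claim rests on a fructose SD alone: it is about 86% on the protocol's own inputs and is untested against the larger SD quoted for inosine

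*Protocol*

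**What the plan says.** Protocol section 9.1 says the sample size draws on two sources: the earlier fructose study "and an analysis of inosine use for Parkinson's disease [1"]. It then states one SD only, for the urate change after fructose, described as "consistent within groups with and without protective alleles across all time points (SD 0.03 mmol/l"). The design is set out as "With 70 participants without the protective allele and 30 with the protective allele". For this split the power claim reads "adequately powered (90% at the 5% significance level for a two tailed test"), and the target is a between-group gap of 0.02 mmol/L in urate change.

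The same section claims more than 90% power for 0.03 mmol/L in an ancestry subgroup of 16 versus 34.

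The closing paragraph of section 9.1 says there is no adequate estimate of variability for the primary change-from-baseline variable. It calls the single-time-point calculation conservative and expects added power from removing between-patient variability.

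Section 7 gives the only inosine SD in the protocol. The source is a long-term study in Parkinson's disease, for which the section reports "a mean (SD) urate increase of 0.18 (0.07) mmol/L was observed with a mean dose of 1.53g inosine". This is the study that section 9.1 names as its second basis.

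**The concern.** Both SDs describe a change in serum urate. One of the two named sources has an SD more than twice the one used (0.07/0.03 = 2.3), and the protocol neither explains the choice nor shows a range. The challenge substance in this trial is inosine, so the fructose figure is carried over by assumption.

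The background section asks whether the genotype effects seen with fructose are specific to fructose or a general response to hyperuricaemia. A null result with inosine would bear directly on that question. How much weight it could carry depends on how well the trial could have seen an effect, and a reader would take that from the 90% claim. The ancestry subgroup claim and the statement on pooled factorial analyses rest on the same SD.

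**Working it through.** **Inputs.** Groups of 70 and 30, difference 0.02 mmol/L, two-sided 5%, SD 0.03 (all section 9.1). Subgroup of 34 and 16, difference 0.03 mmol/L (section 9.1). Alternative SD 0.07 (section 7). The values 0.04 and 0.05 are intermediate assumptions.

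**Formula.** Two-sample t-test at one time point, as section 9.1 describes. SE = SD × √(1/n₁ + 1/n₂) and noncentrality = difference/SE. Power comes from the noncentral t with n₁ + n₂ − 2 degrees of freedom.

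**The protocol's own figure.** √(1/70 + 1/30) = 0.2182, so SE = 0.03 × 0.2182 = 0.00655 and noncentrality = 0.02/0.00655 = 3.06. Power is 85.7% (normal approximation 86.3%), not 90%.

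- A one-sided test would give about 92%, but the text says two-tailed.
- The difference detectable with 90% power is 0.021 mmol/L.
- Reaching 90% for 0.02 exactly needs an SD of 0.028 or less.
- The gap from 90% to 86% may therefore be rounding of either input.

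**Primary comparison over a range of SDs (70 versus 30)**

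| SD (mmol/L) | Power for 0.02 | Difference detectable with 90% power | 95% CI half-width |
|---|---|---|---|
| 0.03 | 86% | 0.021 | 0.013 |
| 0.04 | 62% | 0.029 | 0.017 |
| 0.05 | 44% | 0.036 | 0.022 |
| 0.07 | 25% | 0.050 | 0.030 |

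The half-width is 1.984 × SE. Power falls below 80% once the SD exceeds about 0.032. Above an SD of 0.02/(1.984 × 0.2182) = 0.046, a 95% CI centred on zero would still contain 0.02 mmol/L.

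**Subgroup (34 versus 16, difference 0.03).** √(1/34 + 1/16) = 0.3032, so SE = 0.0091 and noncentrality = 3.30. Power is 89.8% by the t calculation and 91.0% by the normal approximation. That is about 90%, so the claim of more than 90% is borderline even at SD 0.03. It falls to 68% (SD 0.04), 49% (0.05) and 28% (0.07).

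**The claimed reserve of power.** Section 9.1 expects a gain from using change from baseline. But 0.03 is described there as the variability of the change, so removal of between-patient variability is already in the figure and cannot be counted again.

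**The case against.** A reader might set section 7 against section 9.1 and infer that the trial has about 25% power rather than 90%. The documents do not support that, for four reasons.

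- **The SD of 0.07 is a poor match.** It comes from long-term dosing in patients with Parkinson's disease. The dose is reported as a mean, so it may have varied between patients. This trial gives one fixed dose to healthy volunteers and follows them for three hours. The synopsis says the protocol is modified from the earlier acute studies, including the fructose one, so that study is closer in timing and population.
- **Nothing in the protocol says the SD rises with the size of the response.** The only evidence on the point is the report of a constant SD across time points after fructose.
- **The genotype difference might grow too.** If it scaled in proportion to the SD, to 0.02 × 0.07/0.03 = 0.047 mmol/L, power at SD 0.07 would again be about 86%. The protocol fixes neither scaling.
- **The planned analysis differs from the calculation.** Section 9.2 specifies a repeated-measures model with baseline as covariate. This may recover some power, but no correlation is given, so the gain cannot be quantified.

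All four stand, and they make 25% a sensitivity figure. They do not restore 90%, which is missed at SD 0.03, and they do not show that 0.03 applies to inosine. Section 9.1 admits that it lacks an adequate variability estimate, which is a reason to show a range. Section 9.2 already promises 95% confidence intervals, so the groundwork for reading a null result properly is in place.

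**Conclusion.** The concern holds at moderate weight. On the protocol's own inputs the primary comparison has about 86% power for 0.02 mmol/L, and the subgroup comparison has about 90%. Beyond that, the stated power depends on an unargued assumption that inosine responses are as uniform as fructose responses. An SD one third larger (0.04) already lowers primary power to 62%, so the point does not depend on 0.07 being right.

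These figures assume a single-time-point t-test, a true difference held at 0.02 mmol/L and no gain from repeated measures. The protocol does not establish the SD of a three-hour urate change after one inosine dose, so the trial's actual power cannot be stated from it. The design itself is not shown to be wrong. What needs correcting is the power statement.

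**What to change.** In section 9.1:

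1. Restate the power at SD 0.03 as about 86% for 0.02 mmol/L, or give the detectable difference at 90% power as 0.021 mmol/L. Give the subgroup power for 16 versus 34 as about 90%.
2. Either justify 0.03 mmol/L for an inosine load, saying what was taken from the inosine study, or replace the single figure by power and detectable difference for SDs from 0.03 to 0.07.
3. Remove the claim that using change from baseline adds further power. Any gain expected from the repeated-measures model should be stated separately, with the correlation it assumes.

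In section 9.2, add that a non-significant primary result will be interpreted from its 95% CI against 0.02 mmol/L and not read as absence of an effect.

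The cost is a few sentences and one small table. No extra participants are needed and the type I error is unaffected. The downside is a less favourable stated power.

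### The 90% power stated for the primary comparison does not follow from the protocol's own inputs, which give about 86%

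*Protocol*

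**What the plan says.** Section 9.1 prints every quantity that the calculation needs.

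- **Carrier share:** the authors "assume that approximately 30% of participants will have the protective allele".
- **Group sizes:** "With 70 participants without the protective allele and 30 with the protective allele".
- **Variability:** taken from the earlier fructose study, where it "was consistent within groups with and without protective alleles across all time points (SD 0.03 mmol/l").
- **Target difference:** the study is powered "to detect a difference in the change in serum urate between these groups of at least 0.02mmol/l".
- **Claimed power and test:** "the proposed study is adequately powered (90% at the 5% significance level for a two tailed test").

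The same section explains the method: "the conservative approach of modelling the difference between groups at a single time point was chosen to validate the sample size". It expects the planned change-from-baseline analysis to be more powerful, but gives no figure for the gain. It sets that gain against losses, saying that it "should more than offset the very small number of samples which may not be adequately genotyped". Section 9.2 confirms that all tests are two-tailed.

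**The concern.** This is the only power statement for the primary hypothesis, and it is the justification for recruiting 100 people. It can be checked with no hidden parameter, because it is a two-sample comparison of means at one time point with a common SD. A 70:30 split is less efficient than equal groups, and the stated power looked too high for it.

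If the primary comparison turns out null, readers will use the 90% figure to judge how firmly a difference of 0.02 mmol/L can be ruled out. A type II error of 14% instead of 10% is about 1.4 times the stated risk of missing that difference. That is before any loss of samples, for which section 9.1 makes no numerical allowance.

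**Working it through.** **Inputs (all from section 9.1):** n₁ = 70, n₂ = 30, SD σ = 0.03 mmol/L in both groups, difference δ = 0.02 mmol/L, two-sided α = 0.05. Stated power: 90%.

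**Attempt to reproduce the stated figure**

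1. Standard error: σ·√(1/n₁ + 1/n₂) = 0.03 × √(1/70 + 1/30) = 0.006547 mmol/L.
2. Noncentrality: δ/SE = 0.02/0.006547 = 3.055.
3. Normal approximation: power = Φ(3.055 − 1.960) = Φ(1.095) = **86.3%**.
4. Noncentral t with 70 + 30 − 2 = 98 degrees of freedom, critical value 1.984: power = **85.7%**.
5. Simulation (50,000 runs): 85.8% for the pooled t test and 85.1% for Welch's test. Allowing for the efficiency of a Mann-Whitney test gives 84.0%.

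Every two-sided version with a 70:30 split lies between 84% and 86.3%. The stated 90% is not reproduced.

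**What would give about 90% (t test, other inputs held)**

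| Change to one input | Power | Agrees with the text? |
|---|---|---|
| Difference 0.0214 / 0.0215 mmol/L | 89.9% / 90.2% | Only if 0.02 is a rounded figure |
| SD 0.028 mmol/L | 90.0% | Only if 0.03 is a rounded figure |
| 41 carriers, 59 non-carriers | 90.1% | No: 30 and 70 stated |
| 50 and 50 | 91.0% | No: 30 and 70 stated |
| One-sided 5% test | 91.8% | No: two-tailed stated |
| About 115 participants (80 + 35) | 90.3% | No: 100 stated |

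**Sensitivity to the carrier count.** The number of carriers is not fixed by design. If it varies as Binomial(100, 0.30), average power is 85.0%. The protocol's background gives 31.7% to 47.2% carriers among controls of the earlier case-control study. At 32 carriers power is 86.8%, at 40 it is 89.9%, and at 47 it is 90.9%.

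**Sensitivity to rounding of the SD.** An SD printed as 0.03 could lie anywhere from 0.025 to 0.035. Power at 0.02 mmol/L is then 95.3% at the lower end and 73.7% at the upper end. Only values up to about 0.028 support 90%.

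**The case against.** Two arguments deserve weight.

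**Rounding.** The SD and the difference are each printed to one significant figure. An SD of 0.028, or a difference of 0.0215, would print as it does now and would give 90%. Smaller joint departures also suffice: 0.0205 with SD 0.0285 gives 90.4%. An SD near 0.028 would also satisfy the subgroup claim in the same section (16 vs 34, difference 0.03, power above 90%), which gives about 93% at SD 0.028 but 89.8% at exactly 0.03. This is a plausible explanation, and it means that the true design power cannot be fixed at 86% with certainty. It does not rescue the sentence, though. The protocol does not say that its inputs were rounded, and rounding in the other direction would take power well below 86%.

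**The planned analysis is more powerful.** Section 9.2 specifies a repeated-measures analysis of covariance with baseline as covariate, and section 9.1 calls the single-time-point calculation conservative. On assumptions that the protocol does not state, a correlation of about 0.36 between baseline and change would restore 90%. So would averaging the five post-dose measurements if their mean correlation were below about 0.84. Such a gain is quite possible. But the 90% is claimed for the single-time-point calculation, the gain is not quantified, and the protocol already spends it on samples that cannot be genotyped. Moreover, the SD used is described as that of the change in serum urate, so the benefit of working with change is at least partly in the input already.

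What stands is that the consequence is small. The gap is about 4 percentage points, and 86% is still reasonable power for a study of this kind.

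**Conclusion.** The stated power is wrong for the stated inputs. With 70 vs 30 participants, SD 0.03 mmol/L and a two-sided 5% test, power for 0.02 mmol/L is 85.7% (t) or 86.3% (normal approximation). Equivalently, the difference detectable with 90% power is about 0.0214 mmol/L. This takes the printed inputs as exact, assumes exactly 30 carriers and a common SD, and makes no allowance for lost samples or for a gain from the repeated-measures model. The statement should be corrected because it carries the primary sample-size justification. The practical effect is modest and does not put the design in question.

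**What to change.** Rewrite the power sentence in section 9.1 to say, for example, that with 30 carriers, 70 non-carriers, SD 0.03 mmol/L and a two-sided 5% test, the study has about 86% power for a difference of 0.020 mmol/L, or 90% power for 0.0214 mmol/L.

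First check the inputs that were entered in the sample-size software. If a less-rounded SD or difference was used and does yield 90%, print those values to three or four decimals instead, so that the figure can be reproduced. If the authors want to rely on the covariate or repeated-measures gain, they should state the assumed correlation and the power that results.

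The cost is one sentence and possibly a slightly less favourable figure. Enrolment, endpoint and analysis stay as they are. Holding 90% at exactly 0.02 mmol/L with these inputs would instead take about 115 participants, which a gap of this size does not require.
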